## Abstract

**Background:**

Only a small proportion of older patients with generalized anxiety disorder (GAD) seek professional help. Difficulties in accessing treatment may contribute to this problem. Guided self-help based on the principles of cognitive-behavioral therapy (GSH-CBT) is one way of promoting access to psychological treatment. Moreover, because the therapist’s role in GSH-CBT is limited to supporting the patient, this role could be assumed by trained and supervised lay providers (LPs) instead of licensed providers. The main goal of this study is to evaluate the efficacy of GSH-CBT guided by LPs for primary threshold or subthreshold GAD in older adults.

**Methods:**

We will conduct a multisite randomized controlled trial comparing an experimental group receiving GSH-CBT guided by LPs (*n* = 45) to a wait-list control group (*n* = 45). Treatment will last 15 weeks and will be based on a participant’s manual. Weekly telephone sessions with LPs (30 min maximum) will be limited to providing support. Data will be obtained through clinician evaluations and self-assessment questionnaires. Primary outcomes will be the tendency to worry and severity of GAD symptoms. Secondary outcomes will be anxiety symptoms, sleep difficulties, functional deficit, diagnosis of GAD, and cognitive difficulties. For the experimental group, measurements will take place at pre- and post-treatment and at 6 and 12 months post-treatment. For the control group, three evaluations are planned: two pre-treatment evaluations (before and after the waiting period) and after receiving treatment (post-treatment). The efficacy of GSH-CBT will be established by comparing the change in the two groups on the primary outcomes.

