The main goal of this study is to evaluate the efficacy of GSH-CBT guided by LPs for generalized anxiety (i.e., threshold or subthreshold GAD) in older adults. Persons with subthreshold GAD will be included because of its high prevalence [4] and to reinforce the applicability of the findings to a broader and more representative clinical population. The project is a multisite randomized controlled trial comparing an experimental group receiving GSH-CBT guided by LPs to a wait-list control group. The project serves to verify that GSH-CBT is useful and effective and is a key preliminary step to future studies on this treatment, including a larger and more complex randomized controlled trial involving other treatment conditions. Specifically, this project aims to:
Evaluate the effects of treatment on:
i.GAD symptomsii.The psychological mechanisms targeted by the treatment (intolerance to uncertainty, negative problem orientation, cognitive avoidance and perception of the usefulness of worrying)iii.GAD diagnosis and other variables associated with GAD (general symptoms of anxiety, depression, sleep difficulties, disability, and cognitive difficulties)Determine if treatment effects are maintained at 6 and 12 months post-treatment

The hypothesis is that the experimental group will show a significantly greater improvement than the wait-list group on GAD symptoms, as well as psychological mechanisms targeted by treatment and other variables associated with GAD.

Secondary goals are to identify variables (e.g., participants’ characteristics, motivation for entering treatment, credibility of treatment, expectancies about improvement, and working alliance between participants and LPs) associated with improvement during treatment and to document perception of treatment by participants and LPs.

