### Participants

A power analysis was performed based on the Penn State Worry Questionnaire (PSWQ [39]), which is traditionally used as the primary measure of change in studies of CBT for GAD with older adults. Assuming an effect size of .65 (difference in standard deviations between the scores of the treatment group and the wait-list group with telephone support, based on the work of other researchers [41] and a conservative estimate), an alpha threshold of .05 and power of .80, 90 participants are required (45 in each group). In anticipation of an estimated 30% drop-out rate based on previous work [41], a total of 130 people will be admitted to the study (accepted for treatment) in order to obtain the required number of 90. The maximum proportion of participants with a diagnosis of subthreshold GAD will be set at 40% of the sample. This percentage is similar to that in the study by Jones et al. [25] and reflects the priority given to GAD.

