#### Primary outcome measures

These measures will evaluate the symptoms of GAD. The PSWQ will be used to measure the tendency to worry. Statements are rated on a scale ranging from 1 to 5 and a higher total score indicates a greater tendency to worry. The psychometric qualities of the PSWQ with older adults are satisfactory [46]. The GAD-7 [23] will be used to assess the severity of GAD symptoms. GAD-7 statements are answered on a scale ranging from 0 to 3 and a higher total score suggests greater severity. Wild et al. [47] have shown the validity of the GAD-7 for older adults.

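### Two equally ranked primary outcomes (PSWQ and GAD-7) carry the efficacy verdict, but the stated alpha and power cover the PSWQ alone and no rule says how the two results combine

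*Protocol article*

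**What the plan says.** The abstract (Methods) names two primary outcomes: "Primary outcomes will be the tendency to worry and severity of GAD symptoms". It then says how the trial will be judged: "The efficacy of GSH-CBT will be established by comparing the change in the two groups on the primary outcomes".

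The section Primary outcome measures assigns the instruments without ranking them: "The PSWQ will be used to measure the tendency to worry" and "The GAD-7 [23] will be used to assess the severity of GAD symptoms".

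The hypothesis at the end of the Background is worded on the construct, not on a scale: "The hypothesis is that the experimental group will show a significantly greater improvement than the wait-list group on GAD symptoms".

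The sample size (Participants) rests on one scale: "A power analysis was performed based on the Penn State Worry Questionnaire". With an effect size of .65, it continues: "an alpha threshold of .05 and power of .80, 90 participants are required (45 in each group"). This is the only alpha in the article. The same section calls the PSWQ the customary primary measure in this field, but does not place it above the GAD-7 in this trial.

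The section Data management and analysis plans repeated measures ANOVA on most outcome measures. It gives no test-level alpha, order of testing, alpha split or rule for combining the two primary results.

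**The concern.** The article states how efficacy will be decided, and that statement can be read in two ways. Either significance on one of the two scales is enough, or both must be significant. The readings give opposite verdicts when exactly one scale is significant.

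They also have different operating characteristics. Under the first, the chance of a false efficacy claim exceeds .05 if each scale is tested at .05. Under the second, the error rate is protected, but the power that matters is the power to succeed on both scales, and no effect size is given for the GAD-7. Neither reading delivers both of the stated design figures, alpha .05 and power .80, for the efficacy claim as worded. If the choice is made after the data are seen, it can be made to suit the result.

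**Working it through.** **Inputs from the article:** two primary outcomes; PSWQ effect size d = .65 in SD units; alpha .05; power .80; 45 per arm.

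**Assumptions (not in the article):** two-sided tests; .05 applied to each scale; d = .65 on the GAD-7 as well; a simple two-group comparison of 45 per arm; a range of correlations r between the two test statistics.

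**1. The plan's own figure.** The normal formula is n per arm = 2(z₁₋α/₂ + z₁₋β)²/d².
- At alpha .05: 2(1.960 + 0.842)²/.65² = 37.2, so 38 per arm (39 by the t-test). The stated 45 is not reproduced.
- Power at 45 per arm and alpha .05 is .869 (normal) or .862 (t-test).
- At alpha .025: 2(2.241 + 0.842)²/.65² = 44.99, so 45 per arm.

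The stated size therefore equals the normal-formula size for a two-way Bonferroni split. The article does not say that a split was intended, so this is a coincidence to ask about, not evidence of a rule.

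**2. Either scale is enough, each at two-sided .05.** Family-wise error = 1 − P(|Z₁| < 1.96 and |Z₂| < 1.96). At r = 0 this is 1 − .95² = .0975.

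| r | Family-wise error |
|---|---|
| 0 | .0975 |
| .3 | .0951 |
| .5 | .0907 |
| .7 | .0835 |
| .9 | .0704 |

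**3. Both scales required, each at .05.** A false efficacy claim needs a significant result on every scale, including any on which there is no effect, so its probability is at most .05. Joint power at 45 per arm, with d = .65 on both:

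| r | Normal | From the t-test power of .862 |
|---|---|---|
| 0 | .869² = .756 | .862² = .743 |
| .5 | .786 | .775 |
| .7 | .804 | .794 |

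The t-test column for r > 0 converts .862 to a normal quantile and uses the bivariate normal. If the GAD-7 effect were only .50 (a further assumption), joint power by the normal calculation would be .57 at r = 0 and .64 at r = .7.

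**4. Candidate rules at 45 per arm, d = .65.**
- PSWQ first at .05, then GAD-7 at .05: PSWQ power .862 (t-test); family-wise error at most .05.
- Bonferroni at .025 each: per-outcome power .787 (t-test) or .800 (normal). By the t-test, 47 per arm gives .807.

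**The case against.** The strongest objection is that this is a journal article and the statistical analysis plan is not shown. A multiplicity procedure is commonly left to that plan, and a short analysis section without one is not an error in itself. That stands for the mechanics of adjustment. It does not dispose of the point, because the article itself states how efficacy is decided, makes that depend on two outcomes of equal rank, and supports only one of them with alpha and power. What counts as success is part of the design, and the sentence that sets it is ambiguous.

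A reader might infer that the plan accepts a win on either scale and so runs a 9.75% error rate. The documents do not support that. The .05 appears only in the power analysis, no test-level alpha is stated, and nothing says that either scale is enough. The plural wording and a hypothesis on GAD symptoms as a whole fit a both-required reading at least as well, and under it there is no inflation. Independence is also the least plausible case for two scales that the article uses for symptoms of the same disorder.

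Nor is it right to say that the error rate is uncontrolled or that a one-scale result could not be interpreted. Even under the unfavourable reading with .05 per test, the error is bounded by the figures above, and a reader could apply Bonferroni to two reported p-values.

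A last fair point is that the power figures assume a two-group comparison of 45 per arm. The plan is intention-to-treat repeated measures ANOVA with multiple imputation, and 130 people are to be admitted. With complete data on 65 per arm, t-test power at alpha .025 would be about .92. The figures for 45 per arm describe the stated design target and do not predict the power of the final analysis.

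**Conclusion.** The concern holds as an unspecified decision rule for two co-ranked primary outcomes, only one of which is covered by the stated alpha and power. As written, the plan gives no verdict when one scale is significant and the other is not.

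Its size depends on the reading. If either scale is enough, family-wise error is about 7% to 9.5% over r = .9 to .3; this rests on the assumed two-sided .05 for each scale. If both are required, the gap is in power: .80 is not established for the joint claim, and even an equal effect on the GAD-7 gives about .74 to .76 at r = 0 and reaches about .80 only near r = .7.

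This is a should-fix. It bears on the main efficacy claim, but it is bounded and cheap to repair. That 45 per arm does not follow from the stated alpha, power and effect size is a separate matter, and this point does not depend on it.

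**What to change.** Before analysis, add one sentence to Data management and analysis, and align the abstract with it: the PSWQ, on which the trial was powered, is the first-ranked primary outcome, tested at two-sided .05; the GAD-7 is tested at two-sided .05 only if the PSWQ is significant. This holds family-wise error at .05, keeps PSWQ power at about .86 with 45 per arm, and needs no extra participants. The cost is that a significant GAD-7 result with a non-significant PSWQ would not support an efficacy claim.

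If the investigators want the two scales to stay on an equal footing, use Holm or Bonferroni, starting at two-sided .025. Restate per-outcome power at 45 per arm as about .79 (t-test; .80 by the normal formula), and state the effect size assumed for the GAD-7. If both scales were meant to be required, say so and give the joint power with its assumed GAD-7 effect and correlation. If a rule already exists in the full protocol or analysis plan, stating it in these sections closes the point.

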**Discussion:**

This project will provide evidence on the efficacy of a novel approach to treat GAD in older adults. If effective, it could be implemented on a larger scale and provide many older adults with much needed mental health treatment through an expanded workforce.

**Trial registration:**

The trial was registered at ClinicalTrials.gov, number NCT03768544, on December 7, 2018.

## Background

Generalized anxiety disorder (GAD) is mainly characterized by excessive anxiety and worries that are difficult to control, occurring most days for at least 6 months, and are related to a variety of symptoms and activities. Anxiety and worries are associated with three or more of the following symptoms: agitation or feeling overexcited or fed up, tiredness, difficulty concentrating or memory gaps, irritability, muscle tension and sleep disorders [1]. GAD is one of the most common anxiety disorders in older adults. A 4.6% six-month prevalence rate of GAD has been found in community-dwelling older adults, with the first episode beginning after age 50 in one-quarter of cases [2]. Some researchers have found prevalence rates as high as 7.3% [3]. Subthreshold GAD, typically identified in studies when almost all but a few symptoms are present to meet the diagnostic threshold, is even more prevalent than threshold GAD [4]. The negative impact of GAD in late life, even at a subthreshold level, is significant and includes more disability, poorer quality of life and greater use of health care services [5–7]. Anxiety in older adults often presents with comorbid depression [8] and is associated with insomnia [9], poorer cognitive functioning [10], cardiovascular disease [11], greater suicide risk [12], and higher costs for health care [13].

Despite its deleterious consequences and the availability of effective pharmacological and psychological treatments [14], only a small proportion of older patients with GAD seek and use professional help [15, 16]. Various factors, including limited access to mental health care services, may contribute to the undertreatment of older persons [17]. Older adults are particularly likely to have transportation problems [18], as are those receiving home care services [19] and those living in rural areas who also face a limited supply of services [17]. Travel problems are accentuated by harsh climate and in countries, such as Canada, where large distances often have to be covered to get to services. Problems of access to care services are especially problematic for psychotherapy which typically requires weekly meetings with a psychotherapist. Indeed, travel distance is one of the variables significantly related to the use of psychotherapy by older adults [20].

Guided self-help (GSH) is one way of promoting access to psychological treatment. GSH has been defined as a psychological treatment where the patient takes home a standardized psychological treatment and works through it more or less independently [21]. Whereas psychotherapy is typically based on regular personal interaction with the therapist, in GSH (a) the patient uses step-by-step instructions on how to apply a psychological treatment procedure to himself, (b) the role of the therapist is primarily of supportive or facilitative nature, and (c) the amount of contact between the patient and therapist is minimized [21].

There is evidence, albeit limited, that GSH based on the principles of cognitive-behavior therapy (GSH-CBT) is effective for treating GAD in older adults. A randomized controlled trial by Dear et al. [22] evaluated an 8-week online guided program for older adults with anxiety symptoms. Participants were allocated to either the treatment group (*n* = 35) or to a waitlist control group (*n* = 37). Treatment material was presented in a didactic form combined with case-enhanced learning examples. Therapists attempted to contact participants each week via telephone or a secure internal email-type system and tried to limit contact to 5 to 10 min. Lower scores on measures of symptoms of GAD, assessed with the GAD-7 [23], and depression, assessed with the Patient Health Questionnaire-9 Item (PHQ-9 [24]), were found in the treatment group compared to the waitlist control group at post-treatment and were maintained at 3-month and 12-month follow-ups. Among participants in the treatment group, 16 initially had a diagnosis of GAD compared to only two at 3-month follow-up. The latter finding should be interpreted with caution due to the small number of participants with GAD. Moreover, this diagnosis was not a criterion for participation in the study, the authors did not report GAD data for participants in the control group, and diagnostic assessments were conducted by the therapists. Jones et al. [25] conducted a randomized controlled trial of a 10-week guided internet-delivered treatment for older adults with GAD (63% of the sample) or subclinical GAD. Participants were assigned to the treatment group (*n* = 24) or to a waiting list condition (*n* = 22). Those in the treatment group were provided psycho-educational material and CBT strategies for coping with GAD, including homework exercises to apply the skills. Therapist contact consisted of responding by e-mail to participants once weekly (each e-mail took approximately 15–30 min to compose) and served to provide support, guidance, advice, and encouragement. Faster improvements on the GAD-7 and PHQ-9 were observed for participants in the treatment group compared to those in the waiting list condition. A further reduction of scores on the GAD-7 but not on the PHQ-9 was observed at one-month follow-up. As a partial replication of the treatment effects observed in the randomized controlled trial, participants in the control group who eventually received treatment showed lower scores on the GAD-7 and PHQ-9 at post-treatment compared to post-waitlist but not from post-treatment to one-month follow-up.

Registered and experienced clinical psychologists served as therapists in the study by Dear et al. [22]. In the study by Jones et al. [25], the therapist was a graduate student under supervision who held a MA degree in clinical psychology and was eligible for registration in the province of Saskatchewan, Canada. Compared to psychotherapy, GSH requires less involvement from the therapist whose role is essentially to support the patient. This represents an advantage given that health care systems are struggling to adequately respond to the significant mental health needs associated with an aging population [26]. One of the proposed solutions to this problem is to increase the workforce capable of providing mental health care. In the United States, for example, the Institute of Medicine [26] and others [27, 28] have recommended the development of new models of care within existing services in order to expand their capacity to meet the mental health needs of the elderly. These include procedures for training and supervising an expanded workforce [26]. Thus, it is suggested that persons who are not licensed mental health professionals could be able to provide care under certain conditions with regards to training and supervision. Various terms, such as *paraprofessionals* and *non-licensed providers*, are used in the literature to refer to these persons. They are generally providers with no post-graduate training in a specialized mental health program [29]. In this article, we refer to them as lay providers (LPs).

Several studies have explored the effects of psychotherapy applied by LPs compared to professionals. Reviews of these studies show that LPs obtain positive results when they apply psychotherapy for anxiety and depressive symptoms and that these results are comparable to those obtained by professionals [29, 30]. Stanley et al. [31] conducted a randomized trial of CBT for GAD in older adults comparing bachelor-level LPs with Ph.D.-level expert providers as therapists. Patients who received CBT from either LPs or expert providers showed a greater improvement in the severity of GAD, anxiety, depression, and quality of life than patients receiving standard care. Importantly, improvements on these indicators of mental health did not differ between patients receiving CBT administered by LPs or expert providers and were maintained in both groups at 6- and 12-month follow-ups after the end of treatment [32]. Although the costs of training and supervising LPs are not negligible, the cost of treatment per patient has been shown to be much lower when it is administered by a LP rather than a professional such as a psychologist [27].

The main goal of this study is to evaluate the efficacy of GSH-CBT guided by LPs for generalized anxiety (i.e., threshold or subthreshold GAD) in older adults. Persons with subthreshold GAD will be included because of its high prevalence [4] and to reinforce the applicability of the findings to a broader and more representative clinical population. The project is a multisite randomized controlled trial comparing an experimental group receiving GSH-CBT guided by LPs to a wait-list control group. The project serves to verify that GSH-CBT is useful and effective and is a key preliminary step to future studies on this treatment, including a larger and more complex randomized controlled trial involving other treatment conditions. Specifically, this project aims to:
Evaluate the effects of treatment on:
i.GAD symptomsii.The psychological mechanisms targeted by the treatment (intolerance to uncertainty, negative problem orientation, cognitive avoidance and perception of the usefulness of worrying)iii.GAD diagnosis and other variables associated with GAD (general symptoms of anxiety, depression, sleep difficulties, disability, and cognitive difficulties)Determine if treatment effects are maintained at 6 and 12 months post-treatment

The hypothesis is that the experimental group will show a significantly greater improvement than the wait-list group on GAD symptoms, as well as psychological mechanisms targeted by treatment and other variables associated with GAD.

Secondary goals are to identify variables (e.g., participants’ characteristics, motivation for entering treatment, credibility of treatment, expectancies about improvement, and working alliance between participants and LPs) associated with improvement during treatment and to document perception of treatment by participants and LPs.

## Methods

### Trial design

This is a multisite randomized controlled trial comparing an experimental group receiving GSH-CBT guided by LPs to a wait-list control group. The control group will receive GSH-CBT after the waiting period. Because this is a wait-list condition, we will provide no active treatment to participants in this group during the waiting period. This will also maximize their response to GSH-CBT and allow us to include their data in analyses to identify characteristics associated with improvement during treatment. Data will be collected at pre-treatment, post-treatment and 6 and 12 months post-treatment. A multisite study will allow the recruitment of the required sample and increase the generalizability of the study. Université Laval will act as the study sponsor. The study will take place at three sites (Université Laval, Université de Sherbrooke, and Centre de recherche de l’Institut universitaire de gériatrie de Montréal) and patients at each site will be recruited into both intervention groups. A schematic representation of the randomized controlled trial is shown in Fig. 1.

